### 4. Study procedures

**4.1 Informed Consent Procedures**

Potentially eligible participants attending out-patients diabetes clinics at KCH and GSTT will be given the Patient Information Sheet by the clinician. They will then be given at least 48 hours to consider their participation in the study and discuss the decision with family, friends and their care team. A member of the research team will then contact them by telephone to answer any additional questions, verify their understanding of what is involved and confirm their interest in study participation and to arrange for the screening appointment. If the participant is interested in taking part in the study the researcher will gain written consent and recruit to the study.

For each consent form participants will write their initial next to each statement of the Patient Consent Form and sign next to their name. A suitably trained and experienced member of the research team who is authorised on the Delegation Log will then sign the self-duplicating Patient Consent Form, retain two parts (to be stored securely by the researchers and in the hospital medical notes), and give back one part to be retained by the participant. The right of the participant to refuse to participate without giving reasons will be respected. Recruited participants will be consented prior to any data collection.

All participants are free to withdraw at any time from the study without giving reasons and without prejudicing further treatment. No further data will be collected. Data already collected will still be used in the data analysis unless the participant requests otherwise; this will clearly be outlined in the Participant Information Sheet and itemised in the Patient Consent Form.

**4.2 Screening Procedures**

*Screening Visit* (20-30 minutes)

Potential participants will screened for eligibility using the eligibility checklist. They will then be offered the opportunity to ask questions about the study. If they are eligible and happy to proceed, written consent will be taken.

*Data collection visit 1*

The following baseline data will be collected:

- Blood sample (HbA1c) (OGTT data will be taken from patient record)
- Blood pressure
- Weight, height, waist circumference (BMI at booking will be taken from patient record)
- Demographics
- Quality of life (EuroQol EQ-5D-5L)
- Depression (PHQ9)
- Edinburgh Postnatal Depression Scale
- Body Appreciation Scale
- Dietary Change Motivation Scale
- Three Factor Eating Questionnaire
- **Risk Perception Survey for Developing Diabetes**
- Multiple pass 24 hour diet recall (online)
- Adapted GPAQ physical activity questionnaire
- Sleep questionnaire
- Infant feeding intentions scale
- Accelerometer

*Data collection visit 2* (3 months postpartum)

The following interim data will be collected:

- Blood sample (HbA1c)
- OGTT
- Blood pressure
- Weight, height, waist circumference (BMI at booking will be taken from patient record)
- Demographics
- Quality of life (EuroQol EQ-5D-5L)
- Depression (PHQ9)
- Edinburgh Postnatal Depression Scale
- Body Appreciation Scale
- Dietary Change Motivation Scale
- Three Factor Eating Questionnaire
- **Risk Perception Survey for Developing Diabetes**
- Multiple pass 24 hour diet recall (online)
- Adapted GPAQ physical activity questionnaire
- Sleep questionnaire
- Infant feeding
- Infant data (taken from patient records)
- Accelerometer

*Data collection visit 3* (9 months postpartum)

The following follow-up data will be collected:

- Blood sample (HbA1c)
- OGTT
- Blood pressure
- Weight, height, waist circumference (BMI at booking will be taken from patient record)
- Demographics
- Quality of life (EuroQol EQ-5D-5L)
- Depression (PHQ9)
- Edinburgh Postnatal Depression Scale
- Body Appreciation Scale
- Dietary Change Motivation Scale
- Three Factor Eating Questionnaire
- **Risk Perception Survey for Developing Diabetes**
- Multiple pass 24 hour diet recall (online)
- Adapted GPAQ physical activity questionnaire
- Sleep questionnaire
- Infant feeding
- Infant data (taken from patient records)
- Accelerometer

Interview: 9 months postpartum (1 hour)

A structured interview to explore the following will be conducted by a researcher and take place within four weeks of session 5:

- Reasons for drop-out (if applicable)
- Feedback on and satisfaction with the MI intervention
- Feedback on use of the WhatsApp group and any apps used
- Feedback on using the pedometer
- Acceptability of research procedures, data collection and overall experience of the trial

**4.3 Randomisation Procedures**

Participants will be randomised using a computer-generated random number table in blocks of 10. Randomisation will be supported by the Clinical Trials Unit. Double blinding is not possible because the participants will know if they receive an intervention or not. However, this potential source of bias will be considered in the analysis and would be eliminated in a definitive trial. In order to address attrition bias, participants in the control group will be provided with diabetes and health information at follow-up (after completion of measurements).

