**Figure 1. CONSORT flowchart**

**29-32 weeks' gestation:** Dietician or researcher provide information to potentially eligible participant during group education session. Or clinician providing routine care to approach potentially eligible participants at first clinic appointment - brief verbal and written information given and verbal permission for researcher to contact sought

**Baseline / randomisation visit (29-33 weeks' gestation):** Eligibility confirmed; written informed consent (if not previously obtained); randomisation; demography; questionnaires; anthropometry; blood pressure; blood sample; OGTT, provided with 7 day accelerometer and instructions

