**DECLINED or INELIGIBLE**

Routine demographic data recorded if agreed

**29-33 weeks' gestation:** Eligibility screening, responding to questions about the study and taking informed consent (researcher or clinician conducting routine appointment)

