### 3. Sample Size, Selection and Withdrawal of Subjects

A convenience sample of 60 women with current GDM, 30 in each arm will be recruited. King’s College Hospital antenatal diabetes clinic sees around 200 new patients with GDM a year, equating to 17 a month, and Guy’s and St Thomas’ Hospitals see 700 (58 a month). Participants will be recruited opportunistically at their routine clinic appointment upon diagnosis of GDM, group education session the following week, or at a following clinic visit, by a diabetes nurse, consultant or dietician. We estimate that with a 30% recruitment rate we can recruit our sample within 3 months, or with a 15% recruitment rate we can recruit within 6 months. The intervention will last approximately 12 months (depending on gestational stage at diagnosis – usually this is around 28 weeks but can be earlier), with follow-up stopping at 9 months postpartum. We aim to start recruitment, ethical approval permitting, in March 2018, and finish data collection in September 2019. We expect the data to be analysed by December 2019.

Pregnant women have been chosen because: (1) previous research and our qualitative research indicates this is the best time to recruit women to start providing support, (2) women are already engaged with health services so may be easier to recruit, (3) women may be more receptive to behaviour change support during pregnancy, and (4) the highest cumulative incidence of T2DM after GDM is in the first 5 years postpartum, so any intervention should start as soon as possible after identification of GDM.

Potential participants will be identified by the clinical team working at KCH and GSTT. Potential participants will be given the participant information sheet explaining the purpose of the study. Participants who indicate a potential interest in the study will be given the opportunity to consider their participation in the study before being scanned by the researcher for full eligibility using the eligibility screening form. After screening, if the patient is eligible they will undergo consenting, either on the same day or another day at their convenience. Participants may withdraw their interest in the study at any point during the screening and consenting process and their details will not be stored.

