### 6. Assessment of Safety

We have carefully considered the potential clinical hazards associated with this study. These have been discussed by clinical colleagues not directly involved in the study. There are no major risks involved with participation in this study. The study will have in place the following safety monitoring procedures: an incident log for every patient to record any adverse events; an incident log for all clinical research areas to monitor adherence to study protocol and SOP and for recording any incidents that may occur in the conduct of the study; weekly team meetings to consider any difficulties or potential hazards; and clear line of reporting for any adverse events. All team members have completed the KHP Good Clinical Practice. The clinical team will be advised of the patient’s participation in the study to ensure no contradicting intervention during the study.

The responsibility for the conduct of the study resides with all team members with overall responsibility resting with the Chief Investigator (CI). In addition to the weekly team meetings a monthly trial monitoring committee will be held for the duration of the study. This committee is comprised of: the CI, motivational interviewer, 1 diabetes consultant psychiatrist, 1 diabetes medical consultant, 1 diabetes nurse consultant, 2 researchers, a patient representative and a representative from the CTU.

Ethical issues around provision of information to the usual care group will be addressed by providing patients in this group with information about diabetes and healthy lifestyles after completion of follow-up measurements.

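### The protocol states one fixed block size of 10 and no masking of recruiters, so a recruiter who sees all earlier allocations could deduce up to about 10 of 60 on average

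*Protocol*

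**What the plan says.** Protocol section 4.3 sets the method: "Participants will be randomised using a computer-generated random number table in blocks of 10". It then says "Randomisation will be supported by the Clinical Trials Unit" and "Double blinding is not possible because the participants will know if they receive an intervention or not". It does not say whether the staff who recruit see allocations, whether the block size is kept from them, or when an allocation is released.

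Section 3 gives the size and split: "A convenience sample of 60 women with current GDM, 30 in each arm will be recruited". Women are approached at two hospital services "by a diabetes nurse, consultant or dietician". The CONSORT flowchart lets a researcher or a clinician screen and take consent. It places the following in one baseline visit: "Eligibility confirmed; written informed consent (if not previously obtained); randomisation; demography; questionnaires".

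The Trial Statistics and Analysis section mentions a stratification when it describes adjusted regression. Section 4.3 names no stratification factor and does not say whether there is one list or one per site.

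**The concern.** In a permuted block of known, fixed length, the end of the block can be worked out by counting. When one arm has its five places, every remaining place belongs to the other arm. Custody of the list by the Clinical Trials Unit does not prevent this, because the deduction uses only the block size and past allocations.

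Someone who expects the next allocation can, even without meaning to, influence which woman is approached, encouraged or booked next. If more motivated women enter when the intervention is due, the arms differ at baseline in ways that the planned covariates may not capture. The outcomes most exposed are the preliminary efficacy comparison and the effect size that the study is meant to supply for the definitive trial's power calculation. Attrition compared between arms could also be distorted. Section 4.3 says that the lack of blinding will be considered in the analysis, but that does not address selection at entry.

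**Working it through.** The protocol gives no figure for predictability, so there is none to reproduce.

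**Inputs.** Block size 10 (section 4.3). Total 60, with 30 per arm (section 3). Together these imply 5:5 blocks, and six full blocks if there is one list.

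**Allocations known with certainty, one list, all earlier allocations seen.** With m = 5 per arm, the expected number per block is 2m/(m+1) = 10/6 = 1.67. Enumeration of all C(10,5) = 252 sequences agrees. The forced run at the end of the block has length 1, 2, 3, 4 or 5 in 140, 70, 30, 10 and 2 sequences, so the mean is (140 + 140 + 90 + 40 + 10)/252 = 420/252 = 1.67. Over six blocks this is 6 × 1.67 = 10.0 of 60 (16.7%). The simulated 95% range is 6 to 15.

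**Best guessing (Blackwell–Hodges).** Extra correct guesses per block are 2⁹/252 − 1/2 = 2.03 − 0.50 = 1.53. That gives 6.53 correct out of 10, or 65.3%, and 6 × 1.53 = 9.2 extra correct guesses over 60.

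**Other assumptions (simulation).** Expected certain allocations out of 60:
- separate list at each site: about 8.7;
- four equal strata, each with its own list: about 7.3;
- one shared list, recruiter sees only own-site allocations, sites split 22:78: about 2.2 (the split follows from 200 and 700 patients a year in section 3: 200/900 = 22%);
- the same with a 50:50 split: about 0.3.

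**Varied, undisclosed block sizes.** The observer here sees every earlier allocation on one list and knows the set of possible sizes, but not the size in use. With sizes 8, 10 and 12 chosen at random, about 0.9 of 60 allocations are certain (runs gave 0.8 to 0.9), and the best guess is right about 64.8% of the time.

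**Smaller fixed blocks.** The same formula gives 60/6 × 1.5 = 15 certain allocations for blocks of 6, and 60/4 × 1.33 = 20 for blocks of 4. Shortening a fixed block makes matters worse.

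**The case against.** The strongest objection is that 10 of 60 is an upper case. It needs one list and a recruiter who sees every earlier allocation, and the protocol establishes neither. Recruitment is spread over several kinds of staff at two services. This objection stands, and it is why the figure must be given as a range of about 0.3 to 10.

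A reader might infer that the research team as a whole knows all allocations, because section 6 provides for "weekly team meetings to consider any difficulties or potential hazards". The protocol does not support that. It gives no attendance for those meetings and does not say that allocations are discussed. Nor does section 4.3 say that recruiters are unmasked; it speaks only of participants. Holding eligibility, any outstanding consent and randomisation at one visit makes it likely that the researcher present learns the result, but the text does not say so.

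It is also fair to say that the primary outcome is feasibility, that efficacy is secondary and preliminary, that consent may precede the randomisation visit, and that the gestational window is short. These points limit the harm and the scope for steering a particular woman to a particular place, but they exclude neither. No size of bias in any outcome has been estimated.

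Last, varied blocks hardly change the best-guess rate. That is true: the gain is the loss of certainty, not of all predictability. Unit procedures that are not shown may already control release of allocations, but they cannot undo a block size printed in the protocol.

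**Conclusion.** The weakness is real but minor. Section 4.3 fixes one block size in a trial whose participants know their arm, and it describes nothing that keeps recruiters from counting. For a recruiter who knows the block size and sees all earlier allocations on one list, the expected number of certain allocations is 10 of 60. It is about 7 to 9 with site or stratum lists, and about 0.3 to 2 with own-site knowledge of a shared list. The protocol does not show which case applies.

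A reader might go further and conclude that recruiters will know ten allocations, or that the feasibility findings are compromised. Neither follows. The exposure is conditional. It falls mainly on the secondary efficacy contrast and on the effect size for the definitive trial, and possibly on attrition compared between arms. The feasibility list gives an attrition rate without saying that it is arm-specific. This is a low-severity point, worth acting on because the remedy costs almost nothing.

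**What to change.** In section 4.3, replace the fixed block size with wording such as: *in randomly permuted blocks of randomly varying size, with the sizes held by the Clinical Trials Unit and not disclosed to recruiting staff; each allocation is released only after eligibility and consent are logged.* Do not move to smaller fixed blocks.

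Reconcile section 4.3 with the Trial Statistics and Analysis section: either name the stratification factors and say whether lists are separate, or remove the reference to stratification.

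The cost is a short protocol edit and a setting in the list generator, with no change to sample size or visits. The downside is a possible final imbalance between arms. With blocks of up to 12 on a single list, the difference is at most 12/2 = 6 women, when recruitment ends halfway through a block. With stratified lists it could reach 6 in each list.

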**4.4 Schedule of Treatment for each visit**

Data from consenting patients who meet the inclusion criteria and are randomised to the intervention group will receive the following treatment.

| **Table 1: Face-to-face motivational interviewing (MI) Sessions** |
| --- |
| **Session 1: Diagnosis - 2 weeks post diagnosis of GDM (60 mins)** |
| Focus:   - Allow patient to ventilate and express their thoughts and feelings about the diagnosis and their concerns and health beliefs. - Elicit patient’s understanding of diabetes risk and provide simple explanation- confirm understanding. - Elicit what the patient thinks will reduce their risk and provide menu of potential actions that may reduce risk- explore pros and cons with patient. - Encourage patient to choose areas of action, focus on discrete behaviours such as: consumption of sugary drinks, snacks, fast-food, portion sizes and increasing walking. - Explore importance and confidence of action areas- develop self-efficacy as required. - Set pregnancy lifestyle goals (diet and physical activity) with patient using SMART model. - Get patient to identify what personal and social resources they will use in achieving goals. - Introduce and fit patient with the wearable technology (pedometer). - Introduce participant to WhatsApp group   Materials:   - Prompt-card detailing factors contributing to their risk of diabetes. - Prompt-card benefits to their health in pregnancy and for their baby. - Prompt-card with menu of lifestyle steps they can take in pregnancy. - Credit-card sized summary with key messages and web address for additional support. - Pros and cons of breast feeding in terms of diabetes risk for patient and baby.   Targets:   - Patient understands diabetes risk and contributing factors. - Patient motivation and activation. - Patient identifies diet and activity goals. - Patient is familiar with can use pedometer. - Patient is familiar with and can access WhatsApp group. |
| **Session 2:Third trimester (60 minutes)** |
| Focus:   - Reflect on goals from Session 1 affirming what they have achieved and learning reflectively from their experiences, attending to self-efficacy defects and directing to ongoing goals. - Elicit health beliefs, fears and worries, what is going well and what has gone less well. - Elicit what the patient thinks will be important in reducing their risk after pregnancy. - Share ideas on prevention activities in first 3 months postpartum using prompt cards- reflect on infant and family health context. - Review pedometer use. - Set new SMART goals with patient on prevention activities for first 3 months postpartum. - Review use of WhatsApp group. - Record new patient goals on intervention database and update personal plan. - Explain follow-up support to be provided.   Materials:   - Prompt-card with menu of lifestyle areas for early postpartum, including healthy eating tips, breast feeding and strategies for being active with a young infant.   Targets:   - Patient remains motivated and engaged. - Patient identifies 0-3 month postpartum diet and activity goals. - Patient is using pedometer and WhatsApp group. |
| NB. Pregnancy outcomes will be reviewed prior to progression to session 3. |
| **Session 3: 3 months postpartum (60 minutes)** |
| Content:   - Reflect on birth experience and on early postpartum goals, affirming what they have achieved and learning reflectively from their experiences, attending to self-efficacy defects and directing to ongoing goals. - Elicit what the patient thinks will be important going forward to sustain and adapt their lifestyle as the infant grows and their needs change- e.g. weaning and changing socialisation. - Elicit what social and wider resources can help them. - Elicit ways in which the wider family might develop an enhanced lifestyle. - Share ideas on prevention activities from the 3-6 month period using prompt cards- reflect on infant and family health context. - Set SMART goals with patient on prevention activities for first 3-6 month postpartum period. Goals can either be specific lifestyle goals or if patient is not yet ready for action they can be reflective exercises designed to enhance motivation. - Review goal attainment data and pedometer use and explore with patient strategies to increase steps- set a new target. - Discuss patients weight with them in a positive way and any relevant blood tests. - Explain follow-up support to be provided.   Materials:   - Prompt cards with ideas for healthy eating (smart eating), activity ideas (introducing FITT principles); infant and family nutrition; and strategies for being active with a young infant.   Targets:   - Patient remains motivated and activated. - Patient sets goals for 3-6 month period. - Patient is using the pedometer and WhatsApp group. |
| **Session 4: 6 months postpartum (60 minutes)** |
| Content:   - Reflect on their previous goals and experiences to see what can be learned and support with affirmational feedback. - Elicit what the patient now thinks will be important to reduce their risk and provide menu of potential actions that may reduce risk- explore with patient. - Explore importance and confidence of action areas- develop self-efficacy as required. - If patient is ready progress to setting lifestyle goals (diet and physical activity) with patient using SMART model; if patient is not ready explore further pros and cons of status quo and potential for change with reflective exercises. - Review pedometer use and explore with patient strategies to increase steps- set a new target. - Review use of WhatsApp group. - Explain follow-up support to be provided. - Discuss weight and any relevant blood tests.   Materials:   - Prompt-card with activity strategies reflecting needs of an older infant (6-12 months). - Prompt- card exploring health eating strategies for the infant and whole family.   Targets:   - Patient remains motivated and activated. - Patient identifies resources and strategies that will help them fulfil goals. - Patient sets goals or reflective exercises for 6-9 month period. - Patient is using the pedometer and WhatsApp group. |
| **Session 5: Maintenance Session 9 months postpartum (40 mins)** |
| Content:   - Reflect on their previous goals, experiences and what they have achieved to see what can be learned and support with affirmational feedback. - Elicit what the patient now thinks will be important to in helping them to extend and or maintain their lifestyle changes. - Encourage patient to identify longer term goals and strategies to enable them to maintain a healthy lifestyle for themselves, their infant and their family. - Elicit from patient the strategies they could use to help them know they were remaining on track with their plan. - Review pedometer use and explore with patient if they want to continue using the pedometer to help with their maintenance. - Review use of self-help resources and introduce and discuss with patient how they can use these resources to help them maintain a healthy lifestyle. - Explain follow-up support to be provided. - Discuss weight and any relevant blood tests.   Targets:   - Patient has identified strategies to help them maintain their health changes, together with indicators for recognising if they may be relapsing. - Patient will continue to use the pedometer and WhatsApp group. |

Alongside these sessions, participants will be provided with access to a facilitated ‘WhatsApp’ group, in order to connect with other participants in the trial, allow the opportunity for discussion and peer support.

